# Safety Reporting

## 8.1 Adverse Events (AEs)

An Adverse Event (AE) is defined as any new untoward medical occurrence or worsening of a pre-existing medical condition in a patient or clinical investigation subject administered an investigational product and that does not necessarily have a causal relationship with this treatment. An AE can therefore be any unfavorable and unintended sign (including an abnormal laboratory finding, for example), symptom, or disease temporally associated with the use of investigational product, whether or not considered related to the investigational product.

## 8.2 Serious Adverse Events (SAEs)

SAEs are any of the following untoward medical events:

- Death.
- Life-threatening (defined as an event in which the subject was at risk of death.
- Inpatient hospitalization or causes prolongation of existing hospitalization.
- Persistent or significant disability/incapacity.
- Congenital anomaly/birth defects.

## 8.3 Judgement of AEs/SAEs

All AEs and SAEs must be graded according to the National Cancer CTCAE version no. 3, 09-Aug-2006. The following categories and definitions of causal relationship to study drugs as determined by a physician:

- Related: There is a reasonable causal relationship to study drug administration and AEs and SAEs
- Not Related: There is not a reasonable causal relationship to study drug administration and the AE and SAEs. The expression “reasonable causal relationship” is meant to convey in general that there are facts or other arguments to suggest a positive causal relationship.

## 8.4 Collection and Reporting

Adverse events can be spontaneously reported or elicited during open-ended questioning, examination, or evaluation of a subject (to prevent reporting bias, subjects should not be questioned regarding the specific occurrence of one or more AEs).

If known, the diagnosis of the underlying illness or disorder should be recorded, rather than its individual symptoms. The following information should be captured for all AEs: onset, duration, intensity, seriousness, relationship to study drug, action taken, and treatment required. If treatment for the AE was administered, it should be recorded on the appropriate CRF page. The investigator shall supply the sponsor and Ethics Committee with any additional requested information, notably for reported deaths of subjects. Completion of supplemental CRFs may be requested for AEs and/or laboratory abnormalities that are reported/identified during the course of the study.

# Statistical Considerations

## 9.1 Sample Size Estimation

The sample size is calculated to compare overall survival (OS) between two arms. The sample size was estimated on the basis of the overall survival (OS) of 14.9 mon in the combined group and 8.2 mon in the FOLFOX4 only group, which were obtained from the data of our retrospective cohort of patients. The minimum sample size was 106 for the two groups (two-sided α= 0.05; β = 0.20; power, 80%;10% of patients were added to compensate for any loss to follow-up).

[figure not shown]

**9.2 Populations for Analysis**

Intent-to-treat (ITT) population: any patients assigned to a treatment group by the randomization process, regardless of whether patients received any study treatment or received a different study treatment from which they were randomized. This is the primary data set for the test of overall survival, analyses of secondary efficacy endpoints like TTP, symptom assessment and baseline characteristics.

Per protocol (PP) population: all randomized subjects except for subjects who 1) have wrong diagnosis of cancer; 2) are not treated; 3) are not treated with the study therapy as assigned by the randomization. This is the primary dataset for the test of overall survival.

Safety population: All subjects who received at least one dose of study medications. This is the primary data set for dosing, safety, concomitant medications.

## 9.3 Analysis of Efficacy

OS will be compared between two treatment groups, using a log-rank test procedure at 5% significance level and the survival curves will be estimated using Kaplan-Meier estimates. Additional analyses of survival will include the computation of hazard ratios (HRs) and the estimation of survival functions. The survival hazard ratio of TARA+FOLFOX to placebo + FOLFOX and an associated two-sided 95.0% confidence interval will be computed using unadjusted and adjusted Cox proportional hazards modeling. Cox models will include treatment stratified by the above-mentioned stratification factors, and an adjusted model which will include a pre-defined list of covariates (next paragraph) as well as the above-mentioned stratification factors, all as covariates. The response rater (CR and PR) will be compared between two treatments using Chi-Square Test or Fisher’s Exact Test. Repeated measures ANOVA (if applicable) will be used or two-group t-test/Wilcoxon signed rank test on difference between baseline score and the best score in each scale will be used to compare quality of life between two treatments.

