|  | p | HR | 95%CI | | p | HR | 95%CI | |
| Folfox-placebo | 0.027 | 1.792 | 1.068 | 3.005 | 0.037 | 1.740 | 1.033 | 2.931 |
| Sex | 0.033 | 2.005 | 1.056 | 3.807 | 0.158 | 1.612 | 0.830 | 3.129 |
| Age | 0.060 | 1.644 | 0.980 | 2.758 |  |  |  |  |
| PVTT | 0.191 | 1.429 | 0.836 | 2.440 |  |  |  |  |
| T stage | 0.013 | 1.207 | 1.040 | 1.401 | 0.035 | 1.178 | 1.012 | 1.371 |
| N stage | 0.964 | 0.979 | 0.391 | 2.451 |  |  |  |  |
| Number of metastasis>3 | 0.180 | 1.439 | 0.837 | 2.582 |  |  |  |  |
| Pulmonary metastasis | 0.234 | 0.701 | 0.390 | 1.259 |  |  |  |  |
| Metastatic organs>2 | 0.843 | 0.889 | 0.277 | 2.850 |  |  |  |  |
| HBV-DNA load | 0.332 | 1.361 | 0.731 | 2.533 |  |  |  |  |
| AFP>400 | 0.149 | 1.376 | 0.874 | 2.441 |  |  |  |  |
| TB>17.1 | 0.461 | 1.232 | 0.708 | 2.144 |  |  |  |  |
| ALT>44 | 0.740 | 0.891 | 0.450 | 1.763 |  |  |  |  |
| AST>44 | 0.717 | 1.114 | 0.621 | 2.000 |  |  |  |  |
| WBC>4 | 0.850 | 0.948 | 0.544 | 1.652 |  |  |  |  |
| PLT>100 | 0.302 | 1.361 | 0.758 | 2.443 |  |  |  |  |
| ALBI | 0.420 | 1.225 | 0.748 | 2.008 |  |  |  |  |
| Targeted therapy and /or Immunotherapy beore | 0.629 | 0.851 | 0.441 | 1.640 |  |  |  |  |

Table S2.

Univariate and Multivariable Analysis of DFS

| Variables |  | | Univariate Analysis | | |  | | Multivariable Analysis | | |
| --- | --- | --- | --- | --- | --- | --- | --- | --- | --- | --- |
|  | p | HR | | 95%CI | | p | HR | | 95%CI | |
| Folfox-placebo | 0.027 | 1.579 | | 1.053 | 2.368 | 0.037 | 1.541 | | 1.026 | 2.315 |
| Sex | 0.130 | 1.541 | | 0.881 | 2.696 |  |  | |  |  |
| Age | 0.162 | 1.333 | | 0.891 | 1.996 |  |  | |  |  |
| PVTT | 0.036 | 1.586 | | 1.031 | 2.441 | 0.833 | 0.925 | | 0.446 | 1.917 |
| T stage | 0.008 | 1.175 | | 1.044 | 1.324 | 0.093 | 1.187 | | 0.971 | 1.452 |
| N stage | 0.917 | 1.037 | | 0.521 | 2.067 |  |  | |  |  |
| Number of metastasis>3 | 0.100 | 1.442 | | 0.932 | 2.230 |  |  | |  |  |
| Pulmonary metastasis | 0.620 | 0.882 | | 0.539 | 1.446 |  |  | |  |  |
| Metastatic organs>2 | 0.883 | 0.939 | | 0.409 | 2.157 |  |  | |  |  |
| HBV-DNA load | 0.480 | 1.181 | | 0.744 | 1.874 |  |  | |  |  |
| AFP>400 | 0.073 | 1.448 | | 0.966 | 2.170 |  |  | |  |  |
| TB>17.1 | 0.814 | 1.057 | | 0.669 | 1.669 |  |  | |  |  |
| ALT>44 | 0.419 | 0.796 | | 0.457 | 1.385 |  |  | |  |  |
| AST>44 | 0.445 | 1.195 | | 0.756 | 1.889 |  |  | |  |  |
| WBC>4 | 0.079 | 0.678 | | 0.440 | 1.046 |  |  | |  |  |
| PLT>100 | 0.850 | 1.004 | | 0.671 | 1.622 |  |  | |  |  |

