# Study Design

This is a multicenter, double-blinded, placebo-controlled, randomized clinical trial in advanced HCC patients with extrahepatic metastasis. Subjects will be randomly assigned to one of the two arms, either ATRA+FOLFOX or FOLFOX alone. Our study has been registered at <http://www.chictr.org.cn> (ID: ChiCTR-IIR-17012916).

**
[figure not shown]
**

After screening for eligibility and signing of informed consent, qualified subjects will be randomized in a 1:1 ratio to receive ATRA+FOLFOX4 (Group A) or Placebo + FOLFOX4 (Group B). Randomization will be stratified by site and treatment assignments will remain blinded throughout the study.

Names of Therapeutic Agents:

- All-trans-Retinoic Acid (ATRA)
- Oxaliplatin (OXA)
- 5-Fluorouracil (5FU)
- Leucovorin (LV)

Mode of Administration:

ATRA+FOLFOX4 (Group A): ATRA 20 mg oral 3 times/day for 3 days prior to the initiation of chemo (FOLFOX4). ATRA will be discontinued at the end of FOLFOX4(OXA 85mg/m2 iv day1, LV 200mg/m2 iv day1 and day 2, 5FU 400mg/m2 iv bolus at hour 2 and then 600 mg/m2 iv over 22 hours on day 1 and day 2, once every 2 weeks) and a total of 6 cycles were performed. Placebo+FOLFOX4 (Group B):The placebo (replacing ATRA) will be given orally 3 times/day for 3 days prior to the chemo. The placebo will then be discontinued at the end of FOLFOX4 and a total of 6 cycles were performed. The follow-up phase began once a patient terminated the treatment phase.

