**5.2 Secondary analyses**

The secondary outcomes as mentioned under 4.2 are analyzed as follows:

PFS will be compared between two treatment groups, using a log-rank test procedure at 5% significance level and the survival curves will be estimated using Kaplan-Meier estimates. This analysis is executed based according to the intention-to-treat principle (ITT).

The efficiency (ORR and DCR) will be compared between two treatments using Chi-Square Test or Fisher’s Exact Test. Repeated measures ANOVA (if applicable) will be used or two-group t-test/Wilcoxon signed rank test on difference between baseline score. This analysis is executed based according to the intention-to-treat principle (ITT).

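### The log-rank tests for OS and PFS are specified without site although randomisation is stratified by site, and the covariate list promised for the adjusted OS model is not in the text available

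*Combined protocol and SAP*

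**What the plan says.** **Randomisation.** Protocol, Study Design: "Randomization will be stratified by site". SAP 1.4 repeats this. No other factor is named, and Study Population lists three hospitals.

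**OS.** Protocol 9.3 and SAP 5.1: "OS will be compared between two treatment groups, using a log-rank test procedure at 5% significance level". Neither mentions site at this point. The same paragraph then plans Cox models stratified by the randomisation factors, and an adjusted model that carries those factors as covariates beside a "pre-defined list of covariates (next paragraph").

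**PFS.** SAP 5.2: "PFS will be compared between two treatment groups, using a log-rank test procedure at 5% significance level", with Kaplan-Meier curves and no Cox model. Protocol 9.3 gives no PFS test.

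**The covariate list.** After the pointer, protocol 9.3 moves on to response rate and quality of life, and 9.4 is safety. SAP 5.1 keeps the promise of a pre-defined list, drops the pointer and names no variable.

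**Reported models.** Tables S1 (OS) and S2 (labelled DFS, an endpoint the plan does not define) each show 18 variables univariately and three in a multivariable model.

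**The concern.** A log-rank test is the score test of a Cox model with the same stratification. A site-stratified Cox model therefore belongs with a site-stratified log-rank test. The OS plan pairs that Cox model with a test that does not mention site, so the p-value and the confidence interval can disagree.

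Blocked randomisation within site also makes the arms more alike than the unstratified variance assumes. If sites differ in prognosis, the unstratified test rejects too rarely under the null, and pooling unlike sites dilutes the treatment effect. Both cost power in a trial of only 106 patients.

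The covariates matter for a different reason. An adjusted hazard ratio protects against selective reporting only if its covariates were fixed in advance. In Table S1 the adjusted treatment hazard ratio is 1.740 (1.033 to 2.931, p = 0.037). With a lower limit that close to 1, a reader needs to know how the covariates were chosen.

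**Working it through.** **1. The plan's own sample size.** Protocol 9.1 assumes "14.9 mon in the combined group and 8.2 mon in the FOLFOX4 only group", two-sided 5% and 80% power, and 10% loss.

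- Exponential hazard ratio: 8.2/14.9 = 0.550.
- Freedman events: (1.960 + 0.842)² × [(1 + 0.550)/(1 − 0.550)]² = 93.3, so 94, or 47 per arm.
- Every retained patient assumed to die: 47/0.9 = 52.2, so 53 per arm and 106 in total.

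This matches "The minimum sample size was 106 for the two groups". The point below does not change that number.

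**2. What omitting site costs.** From the plan: 106 patients, 1:1, three sites, control median 8.2 months, hazard ratio 0.550. Assumed: site shares, site hazards, blocks of 4 within site, exponential survival and follow-up time. Set A has 24 months of accrual plus 24 of follow-up (6,000 trials per row). Set B has follow-up uniform over 12 to 36 months (8,000 per row). Rejection is at |Z| > 1.96. Each pair is unstratified / stratified, in per cent.

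| Set, site shares (%) | Site hazards | Type I error | Power | Gain from stratifying (points) |
|---|---|---|---|---|
| A, 50/30/20 | no difference | – | 80.8 / 78.6 | −2.2 |
| A, 50/30/20 | 0.7/1/1.5 | – | 75.7 / 77.8 | +2.1 |
| A, 50/30/20 | 0.6/1/2.0 | – | 70.4 / 76.8 | +6.4 |
| B, equal | 1/1/1 | 5.0 / 5.2 | 75.3 / 73.9 | −1.4 |
| B, equal | 1/1.5/0.67 | 4.2 / 5.4 | 70.8 / 73.4 | +2.6 |
| B, equal | 1/2/0.5 | 3.0 / 5.3 | 61.4 / 72.0 | +10.6 |
| B, equal | 1/3/0.33 | 1.7 / 5.4 | 43.6 / 71.1 | +27.5 |
| B, 70/20/10 | 1/1/1 | 5.1 / 4.9 | 76.2 / 74.8 | −1.4 |
| B, 70/20/10 | 1/1.5/0.67 | 5.0 / 5.5 | 74.6 / 75.3 | +0.7 |
| B, 70/20/10 | 1/2/0.5 | 4.3 / 5.3 | 71.0 / 74.4 | +3.4 |
| B, 70/20/10 | 1/3/0.33 | 2.9 / 5.2 | 63.9 / 74.6 | +10.7 |

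Simulation error in Set B is about √(0.75 × 0.25/8000) = 0.5 points for power and √(0.05 × 0.95/8000) = 0.24 points for type I error. The two 1/3/0.33 rows imply a ninefold hazard spread between hospitals. They serve only as a bound.

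**3. How Tables S1 and S2 select variables.**

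- Table S1, univariate p below 0.05: treatment 0.027, sex 0.033, T stage 0.013. These three, and no others, are in the multivariable model. Age (0.060) is left out.
- Table S2, univariate p below 0.05: treatment 0.027, PVTT 0.036, T stage 0.008. Again exactly these three are entered. AFP (0.073) and WBC (0.079) are left out.

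A 0.05 screen reproduces all 2 × 18 = 36 entry decisions; a 0.10 screen does not. The two models also use different covariates.

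Table S2 shows how unstable such a model can be: "PVTT | 0.036 | 1.586 | | 1.031 | 2.441 | 0.833 | 0.925". PVTT moves from a hazard ratio of 1.586 to 0.925 (p = 0.833), and the T stage interval widens from 1.044–1.324 to 0.971–1.452.

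**The case against.** **The log-rank wording is silent rather than declared unstratified, and site does enter the OS Cox models.** True. But the same paragraph states stratification for Cox and not for the test, so the natural reading is an unstratified test. If a stratified test was meant, the text must say so.

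**The gain is small and rests on assumed site effects.** This largely stands. With moderate site differences the gain is about what stratifying costs when sites do not differ. The larger gains need a hazard spread of more than threefold between sites (0.6 against 2.0).

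**The results are in the same file, so replacing the primary test now would be a post hoc switch.** This stands and shapes the fix.

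A reader might also infer more than the documents support:

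- *That the unstratified test inflates false positives.* In the simulations it rejects at or below about 5% under the null.
- *That test and hazard ratio also disagree for PFS.* SAP 5.2 plans no Cox model for PFS. No adjusted PFS model was promised either, so different covariates in Table S2 breach no plan.
- *That no covariate list exists.* The copy read here lacks what stands between SAP 2.2 and SAP 4, so only its absence from the available text can be shown. The broken pointer in protocol 9.3 stands regardless.
- *That Tables S1 and S2 are the planned adjusted analysis, built by univariate screening.* No selection rule is stated, and nothing identifies these tables as the model planned in 9.3. The screen is a strong inference from the pattern.
- *That the reported models ignored site.* A Cox model stratified by site has no site coefficient, so a missing row shows only that site was not listed as a covariate.

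**Conclusion.** The point holds as an improvement the sponsor should make, not as a flaw that invalidates the primary analysis. Site governs the randomisation and the OS Cox models but is missing from the specified OS and PFS tests, and for OS this separates the p-value from the hazard ratio.

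Stratifying gains about 2 points of power with moderate site effects and 6 to 11 with strong ones. With 70% of patients at one site, those gains fall to about 1 and 3. The price is about 1 to 2 points if sites do not differ. All of this depends on the assumed site hazards, shares, block size and follow-up.

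The covariate point is secondary. The pointer is broken and no list is in the available text. The tables fit a p < 0.05 screen exactly, which suggests, but does not prove, data-driven selection. How far a fixed list would move the adjusted hazard ratio cannot be calculated from the documents. In Table S1 the reported adjustment moves the treatment hazard ratio only from 1.792 to 1.740.

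**What to change.** 1. In protocol 9.3 and SAP 5.1 and 5.2, specify the log-rank test stratified by site for OS and PFS, and name site where the text refers back to stratification factors. Because results are already known, report the stratified test as a labelled sensitivity analysis beside the unstratified one.
2. Publish the pre-defined covariate list and fit that model, with site, for OS. If no list exists, fit one list justified on clinical grounds and label it post hoc, since the univariate p-values are already on display.
3. Label Tables S1 and S2 exploratory, state how their variables were chosen and whether the models were stratified by site, and say whether DFS in Table S2 means the PFS of the plan.

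The cost is wording and a few standard re-runs on data already collected. No sample size changes. The stratified test gives up about 1 to 2 points of power if the sites turn out alike.

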# Study Objectives

1. To determine whether ATRA + FOLFOX can improve the overall survival, progress-free survival, time to progress, symptomatic progress, and health-related quality of life.
2. To determine the safety of ATRA in the combination with FOLFOX.

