# Schedule of Events

| **Visits** | **Enrollment & Randomization** | **M1** | **M2** | **M3** | **M4** | **M5** | **M6** | **M7** | **M8** | **M9** | **M10** | **M11** | **M12** |
| --- | --- | --- | --- | --- | --- | --- | --- | --- | --- | --- | --- | --- | --- |
| **Identification** | X |  |  |  |  |  |  |  |  |  |  |  |  |
| **Screen by inclusion/exclusion criteria** | X |  |  |  |  |  |  |  |  |  |  |  |  |
| **Informed Consent Form** | X |  |  |  |  |  |  |  |  |  |  |  |  |
| **Initial Assessment (history/physical/lab/imaging)** | X |  |  |  |  |  |  |  |  |  |  |  |  |
| **Assessment – History/Physical** | X | X | X | X | X | X | X | X | X | X | X | X | X |
| **CT Scan/MRI** | X | X | X | X | X | X | X | X | X | X | X | X | X |
| **Laboratory Tests** | X | X | X | X | X | X | X | X | X | X | X | X | X |
| **Quality of life Questionnaires** | X | X | X | X | X | X | X | X | X | X | X | X | X |
| **Overall Survival** |  | X | X | X | X | X | X | X | X | X | X | X | X |
| **Tumor Progression Assessment** |  | X | X | X | X | X | X | X | X | X | X | X | X |
| **Concomitant Medication** | X | X | X | X | X | X | X | X | X | X | X | X | X |
| **AEs/SAEs** |  | X | X | X | X | X | X | X | X | X | X | X | X |

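### The fallback quality-of-life comparison names a paired test for two independent arms and, in the protocol, uses each patient's best score, which can modestly favour the longer-lived arm

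*Combined protocol and SAP*

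**What the plan says.** The first study objective includes "symptomatic progress, and health-related quality of life". The Schedule of Events marks "Quality of life Questionnaires" at enrolment and at each month from M1 to M12.

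Protocol 9.3 gives the analysis in one sentence. It starts with "Repeated measures ANOVA (if applicable) will be used" and then offers, as an alternative, a "two-group t-test/Wilcoxon signed rank test on difference between baseline score and the best score in each scale". The stated purpose is that these methods "will be used to compare quality of life between two treatments".

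SAP 5.2 carries the same list of methods inside the paragraph on response rates. Its version ends at "two-group t-test/Wilcoxon signed rank test on difference between baseline score": there is no second score to subtract, and QoL is not mentioned.

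QoL is not among the secondary endpoints in protocol 7.2 or SAP 4.2. SAP 2.1 provides in general terms for multiple imputation of values assumed missing at random or completely at random. The readable text, which does not include SAP section 3, gives no criterion for when the ANOVA is applicable, no assessment window and no rule for QoL after death.

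**The concern.** There are two separate faults in the fallback.

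- **The test.** A signed rank test asks whether paired differences centre on zero. Applied to each patient's baseline-to-best difference, it asks whether scores changed, not whether one arm changed more than the other.
- **The summary measure.** The best of many noisy scores is higher than the best of few. If ATRA prolongs survival as planned, its patients complete more questionnaires and their best scores drift upward with no QoL effect. This fault belongs to the summary, so correcting the test does not remove it.

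At stake is a stated objective of the trial. A modest QoL advantage could be reported that only reflects longer follow-up, and the SAP sentence leaves the analyst to choose test and summary once the data are in hand.

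**Working it through.** **1. Inputs.** Planned survival is "14.9 mon in the combined group and 8.2 mon in the FOLFOX4 only group" (protocol 9.1), read here as medians. "The minimum sample size was 106 for the two groups", with 1:1 allocation, gives 53 per arm. Questionnaires are monthly, M1 to M12.

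**2. The plan's own figure.** No figure is stated for QoL. The 106 can be reproduced: HR = 8.2/14.9 = 0.550. Freedman's formula gives (1.96 + 0.84)² × [(1 + 0.550)/(1 − 0.550)]² ≈ 94. Then 47 per arm / 0.9 = 52.2, rounded up to 53, and 2 × 53 = 106. It is used here only to set the arm size.

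**3. The signed rank test.** The arms are independent, so no patient in one is paired with a patient in the other. In the simulation below, with flat mean scores and nobody truly improving, a within-arm signed rank test on best minus baseline rejected in about 100% of trials in both arms. It cannot distinguish the arms.

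**4. Questionnaires per patient.** Under exponential survival with median m, the expected number completed is the sum over t = 1 to 12 of 2^(−t/m):

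- m = 14.9: 8.98
- m = 8.2: 7.23

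**5. Effect on the best score.** Simulated trials had 53 per arm, normal scores with the same mean in both arms, every questionnaire completed while alive, and a two-sample t-test on best of M1-M12 minus baseline. Below, the within-patient correlation is 0.5, the unit is the SD of a single score, and there are 1,500 trials per row.

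| Mean score per month | Survival medians | Spurious difference (SD) | Rejection at nominal 5% |
| --- | --- | --- | --- |
| flat | 14.9 v 8.2 | 0.11 | 8.7% |
| falls 0.05 SD | 14.9 v 8.2 | 0.06 | 6.2% |
| falls 0.1 SD | 14.9 v 8.2 | 0.06 | 6.5% |
| falls 0.2 SD | 14.9 v 8.2 | 0.03 | 4.3% |
| rises 0.05 SD | 14.9 v 8.2 | 0.16 | 13.2% |
| flat | 8.2 v 8.2 | 0.01 | 4.8% |

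Simulation error near 8% is about 1.96 × √(0.08 × 0.92/1,500) = 1.4 percentage points.

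With flat scores, 8.4 of the 8.7 points favoured the longer-lived arm. Varying the correlation from 0.9 to 0.3 moved the difference from 0.05 to 0.13 SD and left rejection at 8-9%. The rank-sum test on the same data also rejected in 8-9%.

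Runs of 4,000 trials with within-patient SD 0.5 to 1.0 of the between-patient SD gave 6.2-7.5%, 5.7-5.9% and 5.0-5.7% for the three rates of fall.

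**6. A fixed early visit.** Alive at M3: 2^(−3/14.9) = 0.87 v 2^(−3/8.2) = 0.78.

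**The case against.** The strongest reply is that the signed rank test is only one of three named options. Repeated measures ANOVA comes first, the two-group t-test is a valid two-sample test, and the sentence states a between-treatment purpose, so signed rank may be a slip for rank-sum. This stands as a limit: a reader might infer that QoL is simply to be compared by a paired test, and the documents do not say that. It does not excuse the wording, which the SAP repeats, and the t-test still carries the best-score bias.

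Second, the best score appears only in the protocol. That is correct. The SAP does not repeat the bias; its defect is an unfinished sentence.

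Third, the size depends on how QoL changes over time, which the documents do not give. That also stands. With a steep fall the excess nearly vanishes, and even at 8-9% more than nine null trials in ten do not reject. The inference that the plan tends to produce a false QoL benefit is too strong.

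Fourth, a reader might calculate that only 57% v 36% are alive at M12 and conclude that the ANOVA discards 43% v 64% of patients. The documents do not support this: SAP 2.1 provides for multiple imputation, and no text requires all 12 visits to be complete. What remains is that general imputation, applied without a rule for death, could create scores for patients who have died.

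**Conclusion.** The concern holds for the fallback analysis. Naming the signed rank test is an error on the face of protocol 9.3 and SAP 5.2, and needs no assumption to establish. The SAP sentence cannot be carried out as written.

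The best-score bias is real in direction and modest in size: about 8-9% rejection and a spurious difference of about 0.07-0.15 SD (between-patient) with flat scores, about 5-8% if scores fall by 0.05-0.2 SD a month, and about 10-15% if they rise by 0.05 SD a month. These figures rest on exponential survival, 14.9 and 8.2 months as medians, normal scores, full completion while alive and no true QoL effect. If survival is equal, the bias disappears.

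The reach is limited. QoL is part of the first objective but not a listed secondary endpoint. A reader might infer a threat to the trial's main conclusion, but the overall survival test does not use these data. The correction should be made, with moderate confidence in the size of the bias.

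**What to change.** In protocol 9.3 and SAP 5.2:

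- Replace the signed rank test with the Wilcoxon rank-sum test, and name QoL in the SAP sentence.
- Delete the best score. Compare change from baseline at one fixed early visit, for example M3.
- Preferably take that contrast from a mixed model for repeated measures on all scores collected while alive, with baseline score, arm, visit, arm-by-visit and site. An unstructured covariance over 12 visits has 12 × 13/2 = 78 parameters for 106 patients, so allow a more parsimonious structure.
- State that scores after death are not imputed and that the estimate applies to patients while alive. Report the number alive and assessed by arm at each visit.

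The cost is wording and one model with a stated covariance choice; the monthly questionnaires are already scheduled. There are two downsides. A fixed-visit estimate may look smaller than a best-score change, and some survivor selection remains at M3, since the arms already differ in the proportion alive.

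### No baseline adjustment is specified for the quality of life comparison, although the baseline score is scheduled; adding it is a free precision gain of unknown size

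*Combined protocol and SAP*

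**What the plan says.** Health-related quality of life is part of the first study objective, which ends with "symptomatic progress, and health-related quality of life". It is not among the secondary endpoints in protocol 7.2 or SAP 4.2, and no target difference, SD or power is given for it.

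Protocol 9.3 leaves the method open: "Repeated measures ANOVA (if applicable) will be used or two-group t-test/Wilcoxon signed rank" and then "test on difference between baseline score and the best score in each scale will be used to compare quality of life between two treatments". The first option is thus an unspecified repeated measures ANOVA. The second is an unadjusted comparison of change from baseline to the best score.

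SAP 5.2 has a similar sentence in its response-rate paragraph: "Repeated measures ANOVA (if applicable) will be used or two-group t-test/Wilcoxon signed rank test on difference between baseline score". It stops there, naming neither quality of life nor the later score.

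The Schedule of Events has a row for "Quality of life Questionnaires" marked at enrolment and at each of months 1 to 12. The plan does use covariates for survival, where the Cox analysis has "an adjusted model which will include a pre-defined list of covariates (next paragraph) as well as the above-mentioned stratification factors, all as covariates". No such model is stated for quality of life. The SAP text between sections 2.2 and 4 was not available to check.

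**The concern.** A change score fixes the coefficient on the baseline value at 1. A model with baseline as a covariate estimates that coefficient. When the true slope is below 1, as it usually is for a noisy questionnaire score, the change score carries surplus baseline noise into the arm comparison.

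The repeated measures ANOVA does not clearly close the gap. No baseline covariate is named for it. If baseline is one of its time points, the arm main effect averages in a visit on which treatment cannot have acted, while an arm-by-time contrast against baseline is itself a comparison of changes.

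At stake is the precision of one part of objective 1. The trial was sized for survival, and deaths will thin the questionnaire data, so there is little precision to spare.

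**Working it through.** **Inputs**
- 106 patients allocated 1:1, so 53 per arm (protocol 9.1 and Study Design; SAP 1.6).
- One baseline and 12 later questionnaires (Schedule of Events).
- Correlation r between baseline and follow-up score: not in the documents; assumed 0.3 to 0.7.
- SDs s0 (baseline) and s1 (follow-up): not in the documents; assumed equal, then varied.

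**Step 1: the plan's own figure.** There is none for quality of life. The 106 is for overall survival. It is reproduced by the Freedman formula with HR = 8.2/14.9 = 0.5503: (1.960 + 0.842)² × (1.5503/0.4497)² = 7.849 × 11.89 = 93.3. That rounds up to 94 events, or 47 per arm. Then 47/0.9 = 52.2, rounded up to 53 per arm, gives 106, taking one event per patient. The 53 per arm therefore says nothing about quality of life precision.

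**Step 2: direction.** Per-patient variances for one follow-up score:
- change score: s0² + s1² − 2·r·s0·s1
- baseline-adjusted: s1²(1 − r²)
- difference: (s0 − r·s1)²

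The difference is never negative. It is zero when the slope r·s1/s0 equals 1. The cost of estimating the slope is one degree of freedom, negligible with 106 patients.

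**Step 3: illustrative size, equal SDs.** The ratio of adjusted to change-score variance is (1 − r²)/(2(1 − r)) = (1 + r)/2. The detectable difference at 80% power, in SDs of a single score, is (1.960 + 0.842) × √V × √(2/53), with V the per-patient variance and every patient contributing.

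| r | V, change | V, adjusted | Ratio | Variance cut | SE cut | Detectable difference, change → adjusted |
| --- | --- | --- | --- | --- | --- | --- |
| 0.3 | 1.40 | 0.91 | 0.65 | 35% | 19% | 0.64 → 0.52 |
| 0.5 | 1.00 | 0.75 | 0.75 | 25% | 13% | 0.54 → 0.47 |
| 0.7 | 0.60 | 0.51 | 0.85 | 15% | 8% | 0.42 → 0.39 |

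**Step 4: sensitivity over the same r.** The variance cut is 1 − s²(1 − r²)/(1 + s² − 2rs), with s = s1/s0.
- s = 1.25: 22% at r = 0.3, 11% at 0.5, 2% at 0.7 (the slope at r = 0.7 is 0.875, close to 1).
- s = 0.8: 50%, 43% and 37%.

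Protocol 9.3 uses the best score, to which the single-score formula does not apply directly. It was simulated with normal scores and equal correlation between all visits:
- all 12 visits observed: 53%, 38% and 23%.
- number of visits varying from 1 to 12 (assumed exponential, median 8.2 months): 38%, 27% and 16%.

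The repeated measures ANOVA is not specified well enough to give a figure.

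**The case against.** The strongest reply is that nothing here is an error. Under randomisation an unadjusted two-group test on change scores is unbiased and keeps its type I error, so ANCOVA is a preference. That stands. A reader might infer that chance baseline imbalance makes the planned comparison invalid. It does not: imbalance matters only conditionally on the baselines observed, and the issue is efficiency.

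A reader might also take 15% to 35% as the precision this plan gives away. The documents do not support that. The range needs an assumed correlation, equal SDs and a single follow-up score, and it is on the variance scale. The planned outcome is a best score over up to 12 visits, and repeated measures ANOVA is named first. Step 4 shows the figure running from 2% to 53% under other plausible assumptions.

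Nor should SAP 5.2 be read as an explicit quality of life analysis; linking it to protocol 9.3 is an inference from the similar wording. The Schedule of Events shows that a baseline questionnaire is planned, not that every patient will complete one.

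Finally, quality of life is not a listed secondary endpoint, and the sentence in protocol 9.3 has heavier faults. The best score depends on how many visits a patient completes, and the signed rank test is a paired test that does not compare two independent groups. Both are separate defects. Correcting them alone would still leave the comparison unadjusted.

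**Conclusion.** The point holds as a minor, free improvement. Neither protocol 9.3 nor SAP 5.2 specifies adjustment for the baseline quality of life score, although that score is scheduled at enrolment. In large samples adjustment cannot lose precision, whatever the correlation and SDs. How much it gains cannot be read from the documents. With one follow-up score, equal SDs and an assumed correlation of 0.3 to 0.7, the variance falls by 35% to 15% and the standard error by 19% to 8%. With a slope on baseline near 1 the gain is close to nothing. The validity of the trial and its primary analysis are not affected. The statement that no adjustment is specified is limited to the text available.

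**What to change.** In protocol 9.3 and SAP 5.2, name quality of life explicitly and replace the present choice of tests. Specify a linear mixed model of the scheduled post-baseline scores of each scale. The fixed effects are arm, visit, arm-by-visit, baseline score and site, the last because randomisation is stratified by site. Keep baseline out of the outcome vector. ANCOVA at one named visit, with arm, baseline score and site, is a simpler alternative. Report the adjusted arm difference with its 95% confidence interval.

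Naming the visit or the visit contrast in advance matters, because a phrase such as the post-baseline score is undefined with 12 visits. If the best score were kept as the outcome, adjustment would only sharpen a contrast that still depends on visits completed, so that defect needs its own correction.

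The cost is a wording change in two sections. No patient, visit or form is added.
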